##### The amount of emergency drug used

2.5.2.10

If patients experience exacerbated symptoms such as coughing and expectoration that they cannot tolerate, the use of Compound Methoxyphenamine Capsules is allowed.

### Sample collection

2.6

Blood samples (standard EDTA blood collection) will be collected on day 1 and day 7; these will be subsequently centrifuged to separate plasma and serum, and samples will be frozen at −80 °C.

Sputum samples will be collected from each patient sputum induction using hypertonic saline is performed if participant unable to expectoration, based on Chinese national guideline on diagnosis and management of Cough (30).

All of biological samples will be used for muti-omics analysis to explore the biological mechanisms of YMJD.

### Safety evaluation

2.7

Safety assessments include adverse events, clinical laboratory tests, physical examinations, vital signs, and electrocardiogram (ECG). Vital signs examination, including blood pressure, body temperature, respiration, and pulse, will be collected on the 1, 4 ± 1, and 7 ± 1 days of enrollment. Routine blood and urine tests, liver and kidney function tests and ECGs will be collected on the 1 and 7 ± 1 days of enrollment.

### Participant timeline

2.8

Patients in the trial are required to be recorded four times, with visits at enrollment, day 4, day 7 and day 14. The specific assessments at each visit are detailed in Table 4.

**Table 4 tab4:** Time schedule of enrolment, intervention and outcome measures of the trial.

Study phase	Treatment phase			Follow-up phase
Study day	Day 1	Day 4	Day 7	Day 14
Basic medical history				
Informed consent form	X			
Basic condition	X			
Treatment history	X			
Past medical history	X			
Allergy history	X			
Concomitant medications		X-------------------------------------------X		
Efficacy evaluation				
Chest CT	X		X	
C-reactive protein	X		X	
Serum procalcitonin	X		X	
Interleukin 6	X		X	
Serum amyloid A	X		X	
Efficacy evaluation indicators				
Clinical symptom assessment		X-------------------------------------------X		
Clinical symptom improvement rate on day 4		X		
Improvement rate of single symptoms			X	X
CASA-Q	X		X	X
Improved pneumonia Imaging Absorption Evaluation scale	X		X	
CURB-65 score	X		X	
Dosage and course of antibiotics		X	X	X
Changes in inflammatory indicators	X		X	
TCM Syndrome Points		X------------------------------------------X		
Improvement rate of TCM evidence of efficacy		X	X	X
The amount of emergency drug used		X-----------------------------------------X		
Safety evaluation				
Basic vital signs	X	X	X	
Routine blood test	X		X	
Liver and kidney function tests	X		X	
Routine urine test	X		X	
Urine pregnancy test	If necessary			
ECGs	X		X	
Adverse event assessments		X------------------------------------------X		
Other related work				
Subject screen	X			
Random assignment	X			
Drug distribute	X			
Collect blood and sputum samples	X		X	

### Sample size calculation

2.9

The sample size calculations for this study was determined based on the primary outcome, which is the improvement rate of clinical symptoms on the 4th day of treatment. We estimated the improvement rate based on literature reviews of published studies (24, 31). The improvement rate was assumed to be 78% for the control group and 92.5% for the treatment group. Statistical tests were performed at a two-sided significance level of 0.05. The test power was set to 1-*β* = 80%, and the sample size ratio of the two groups was 1:1. Pass (version 15.0.5) was used for the analysis. A total of 180 patients are planned to be enrolled in this trial. Considering a dropout rate of about 20%, our target sample size is 226 patients, with 113 in each group.

### Statistical analysis

2.10

#### Preset subgroups

2.10.1

We will present subgroups based on the following factors and conduct subgroup analysis on the main efficacy indicators: age, pneumonia severity, TCM syndrome, combined disease, and antibacterial drugs of different classes.

#### Analysis set

2.10.2

The efficacy will be evaluated by Full Analysis Set (FAS) and Per-protocol Set (PPS), and the safety will be evaluated by Safety Set (SS). The FAS includes data from all randomized patients who received at least one dose of the study drug and had at least one post-randomization assessment. The PPS included all patients who adhered to the trial protocol, had no missing baseline variables, had evaluable primary variables, and had no major protocol violations. The SS included all patients who took at least one dose of the study drug and had safety data recorded.

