#### Withdrawal criteria and management

2.2.4

Patients will be required to withdraw for the following reasons.Patients’s condition worsens, requiring discontinuation of the trial.Serious complications, allergic reactions, significant physiological changes that occur during the trial.Using other treatment methods or drugs that are prohibited from being used in combination.Serious adverse events during the study period.Patients are unwilling to continue the trial and ask to withdraw from the trial.Poor subject compliance of patients (such as taking drugs in violation of the prescribed dose, or using prohibited drugs).Poor compliance of patients (trial medication adherence <80% or >120%).Blind release or emergency unblinding.Researchers decided to withdraw the patient from the trial.

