#### Primary outcome

2.5.1

##### Clinical symptom improvement rate on day 4

2.5.1.1

The primary outcome is early clinical response, defined as an improvement in at least two of four symptoms (cough, chest pain, sputum production, dyspnea) without any exacerbation of any symptom within 96 h following the initial dose of study medication in the intention-to-treat population (24).

An improvement in symptoms is defined as a reduction in severity by a minimum of one grading level. Refer to Table 2 for details.

**Table 2 tab2:** Community-acquired pneumonia symptom severity assessment scale.

Symptoms	Asymptomatic	Mild	Moderate	Severe
Cough	No cough	Coughing, but does not interfere with daily activities	Frequent cough that interferes with daily activity	Coughing day and night, most daily activities limited, sleep disrupted
Expectoration	No expectoration	Mild expectoration	Moderate expectoration	Excessive expectoration
Pleurisy pain	No pneumonia-related chest pain	Occasional chest pain during deep breathing, but does not interfere with daily activities	Chest pain during normal breathing, affecting daily activities	Chest pain occurs during rest or shallow breathing, and most daily activities are limited
Dyspnea	No dyspnea	Shortness of breath during intense activities, but does not interfere with daily activities	Frequent dyspnea that interferes with daily activity	Dyspnea occurs during mild activity or at rest, and most daily activities are limited

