#### Interim analysis

2.10.5

This trial will establish an independent Data Monitoring Committee (IDMC), consisting of at least two clinical medical experts and one statistical expert who are independent of the trial. The main responsibility of IDMC is to evaluate interim analysis of efficacy and safety data, and review the results based on data analysis. After the first 114 patients (50%) completed the improvement rate of clinical symptoms on day 4 (including dropout and early termination of treatment), the independent statistical team will strictly follow the preset IDMC regulations, conduct unblinded analysis on the data of these 114 patients according to the interim analysis plan and IDMC requirements, and re-estimate the sample size based on the interim analysis results.

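### The primary outcome is set in the intention-to-treat population, but neither efficacy analysis set is that population, and both can leave out patients lost before day 4

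*Protocol article*

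**What the plan says.** Section 2.5.1.1 (Primary outcome) defines early clinical response as improvement in at least two of four symptoms with no symptom getting worse, "within 96 h following the initial dose of study medication in the intention-to-treat population".

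Section 2.10.2 (Analysis set) names two sets for efficacy, the FAS and the per-protocol set (PPS), and no intention-to-treat set. The FAS takes randomised patients who "received at least one dose of the study drug and had at least one post-randomization assessment". The PPS is narrower: among other conditions, its members must have "had evaluable primary variables, and had no major protocol violations".

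Four other places bear on how these definitions work in practice:

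- Section 2.8 (Participant timeline) schedules four contacts, "with visits at enrollment, day 4, day 7 and day 14".
- Section 2.2.4 (Withdrawal criteria) requires withdrawal of, among others, patients whose "condition worsens, requiring discontinuation of the trial", and of patients with serious adverse events.
- Section 2.9 (Sample size calculation) derives 180 patients from 78% against 92.5% and then states: "Considering a dropout rate of about 20%, our target sample size is 226 patients".
- Section 2.10.5 (Interim analysis) counts the first 114 patients at day 4 "including dropout and early termination of treatment".

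**The concern.** The primary endpoint names one population and the analysis section defines two others. An analysis plan can choose between the FAS and the PPS, but neither choice gives the population in section 2.5.1.1.

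A FAS that needs a dose and one assessment is a common convention. It does little harm when several assessments come before the endpoint. Here the first scheduled post-enrollment visit is the endpoint visit, so the condition falls on the interval in which early failures occur. Some reasons for leaving in that interval are themselves failures, and some may differ by arm: only the active product contains rhubarb (Table 1), and the Discussion foresees that participants may notice differing gastrointestinal effects. Excluding patients for an event after randomisation that is tied to outcome and possibly to arm removes the protection of randomisation from the primary comparison. A missing-data rule applied inside the FAS would not bring these patients back, because they are no longer in it.

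**Working it through.** **1. The plan's own figure.** Inputs from section 2.9: control 78%, treatment 92.5%, two-sided 0.05, power 80%, ratio 1:1, dropout about 20%. With unpooled variance:

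n per arm = (1.960 + 0.842)² × [0.78 × 0.22 + 0.925 × 0.075] / (0.925 − 0.78)² = 7.849 × 0.24098 / 0.021025 = 89.96, so 90 per arm and 180 in total.

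Dropout: 90 / 0.8 = 112.5, so 113 per arm and 226 in total. Both stated figures reproduce.

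**2. Who falls outside both sets.** Take a randomised patient who has taken a dose and leaves before day 4.

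| Situation | All randomised (2.5.1.1) | FAS (2.10.2) | PPS (2.10.2) |
|---|---|---|---|
| Some post-randomisation assessment on record, no day-4 grade | in | in | out |
| No post-randomisation assessment on record | in | out | out |

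A randomised patient who took no dose is also outside the FAS. The interim count in section 2.10.5 keeps dropouts and early terminations, which is closer to the first column than to the FAS.

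**3. Possible bias.** The documents give no loss rates before day 4, so the rates here are assumptions. Let the true response be 78% in both arms (no effect), let a fraction d of an arm be excluded, and let every excluded patient be a failure. The rate seen in the FAS is 0.78 / (1 − d). The rejection rate is the exact two-sided probability that the pooled z-test gives p < 0.05 with 113 randomised per arm.

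| Loss, one arm / other arm | FAS rates | Spurious difference | Rejection under no effect |
|---|---|---|---|
| 5% / 5% | 82.1% / 82.1% | 0 | about 5% |
| 5% / 2% | 82.1% / 79.6% | 2.5 points | about 8% |
| 10% / 5% | 86.7% / 82.1% | 4.6 points | about 15% |

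The arm that loses more failures looks better. If it is the active arm, the bias favours YMJD. If it is the placebo arm, for instance through worsening, the bias goes against YMJD by the same amount.

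**4. Power at 113 per arm under the two readings of 78% and 92.5%.** The calculation is exact binomial power of the pooled z-test.

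- Rates refer to all randomised patients: 88.9%.
- Rates refer to completers, and patients without a day-4 grade count as non-responders. Each rate is multiplied by (1 − loss), with equal loss in both arms:

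| Day-4 loss | Rates | Power |
|---|---|---|
| 2% | 76.4% / 90.7% | 84.0% |
| 5% | 74.1% / 87.9% | 76.3% |
| 10% | 70.2% / 83.3% | 64.7% |

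**The case against.** The strongest reply is that early failures need not disappear. The FAS asks for one post-randomisation assessment, not a day-4 grade. Table 4 shows symptom assessment, concomitant medication and adverse events as continuous bars, and the antibiotic regimens in section 2.4 are those for hospitalised patients. Someone withdrawn for worsening has been observed after randomisation and may count as assessed. This stands, as far as it goes: the article does not say what counts as an assessment. A reader might infer that almost everyone who leaves before day 4 is lost, or that the FAS is nearly a complete-case analysis. The text does not support either. It supports only that patients with no recorded assessment are excluded. How FAS members without a day-4 grade are handled may be settled in an analysis plan that is not shown, and that gap is not part of this point.

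It can also be said that the loss rates are invented and that equal loss does no harm. That is correct for the no-effect case: equal 5% loss gives no bias in the difference. The figures show sensitivity and do not predict what will happen.

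A reader might further infer that the 80% power holds only for completers, since the 20% allowance treats dropouts as removed. Section 2.9 does not say so. It takes its rates from published studies, and one of them is the reference attached to the intention-to-treat definition in section 2.5.1.1. If the rates cover all randomised patients, power is ample. Nor is the 20% tied to day 4: it is a general allowance in a 14-day study, so applying all of it to a 96-hour endpoint would be extreme.

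None of this reconciles section 2.5.1.1 with section 2.10.2.

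**Conclusion.** The point holds as an inconsistency that can affect the primary comparison. The population named for the primary outcome is not among the efficacy sets, and both sets can exclude patients for reasons linked to outcome and arm. The direction of any bias is open. Its size depends on early losses that the documents do not give. Under no true effect, with all lost patients failures, the false-positive rate goes from about 5% (equal loss) to about 8% (5% against 2%) and about 15% (10% against 5%).

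The power consequence is conditional. It is about 89% if 78% and 92.5% are rates in all randomised patients. If they are completer rates and missing grades count as non-response, it is about 84%, 76% and 65% at 2%, 5% and 10% day-4 loss. A flat statement that the trial is underpowered would go beyond the text.

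**What to change.** - In section 2.10.2, make all randomised patients, analysed as randomised, the primary analysis set, so that it matches section 2.5.1.1.
- Count a patient without an evaluable day-4 grade as a non-responder for the primary outcome.
- Keep the FAS as now defined, and the PPS, as sensitivity analyses.
- In section 2.9, state whether 78% and 92.5% are rates in all randomised patients or in completers. If they are completer rates, restate the power for the primary set with an assumed day-4 loss.

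The cost is wording. It should be settled before the unblinded interim at 114 patients, because a choice of primary set made after that could be challenged as data-driven. The fix itself calls for no added patients. The possible downside is a less favourable stated power, slight at small day-4 losses and larger if losses reach the upper end of the range shown.

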#### Analysis method

2.10.3

All analysis and data visualization will be performed using SAS Version 9.4.

For continuous variables, the descriptive statistics will include the count of patients (*n*), along with the mean, median, standard deviation (SD), minimum and maximum values. This model will utilize the changes in indicators from baseline as the dependent variables, while accounting for the treatment groups, random stratification factors, and baseline values as covariates. The least squares mean and the associated 95% confidence intervals will be calculated for the changes from baseline for both the test and control measures, as well as for the differences between the groups, specifically from the test group to the control group.

Categorical data will be presented as frequencies and proportions. The 95% confidence interval for each rate was derived using the Clopper-Pearson method. To assess the differences between the two groups across stratification levels, the Cochran–Mantel–Haenszel (CMH) statistic will be employed, considering the random stratification factors. Furthermore, the stratified Newcombe method, which also accounts for these stratification factors, will be utilized to calculate the rate difference for each indicator from the treatment group compared to the control group, along with its corresponding 95% confidence interval.

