#### Inclusion criteria

2.2.2

Each patient had to satisfy the following inclusion criteria before entry into the study:Patients are between 18 and 80 years of age.Meeting the diagnostic criteria for CAP in the “Guideline of Diagnosis and Treatment for Community-Acquired Pneumonia among Adults in China (released in 2016) (20)”.Meeting the “Guidelines for Traditional Chinese Medicine Diagnosis and Treatment of Community Acquired Pneumonia (2018 Revision) (11) for the “*syndrome of wind-heat invading lung*” or “*syndrome of phlegm-heat obstructing lung*” in Chinese medicine (21).The clinical symptoms should manifest as at least 2 of the following 4 main symptoms: cough, expectoration, dyspnea (shortness of breath), and pleurisy chest pain.Patients with CURB-65 score 0–2 (22).Before recruitment, clear notification and signing of informed consent are required.

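### The primary CMH test and Newcombe interval are valid but leave out baseline symptom count, a likely predictor of the 2-of-4 response; adding it as a stratum is a cheap efficiency gain

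*Protocol article*

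**What the plan says.** Section 2.3 makes age the sole stratification factor for randomisation. Section 2.10.3 carries this into the analysis of rates, which covers the primary outcome: the CMH "statistic will be employed, considering the random stratification factors", and the stratified Newcombe interval for the rate difference uses the same factor. In the same section, the model for continuous outcomes does include the baseline value as a covariate.

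Two other sections matter. Section 2.2.2 sets the entry rule: "The clinical symptoms should manifest as at least 2 of the following 4 main symptoms". Section 2.5.1.1 defines response as "improvement in at least two of four symptoms" with none worse, each improvement being a fall of at least one grade. Symptom count is not a stratum in randomisation or analysis, and it is not among the preset subgroups in 2.10.1.

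**The concern.** Patients enter with two, three or four symptoms. A symptom graded as absent cannot fall a grade, so the hurdle differs by entry status: two out of two, any two of three, or any two of four. Baseline count is therefore a likely predictor of response. Its value is already in hand, because the day-4 endpoint cannot be scored without the baseline grades.

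A predictor left out of the analysis can cost some precision. Because randomisation does not balance the count, a chance difference between arms in the share of two-symptom patients also passes straight into the estimate. The plan adjusts for baseline in the continuous outcomes but not in the one outcome whose definition depends on baseline status.

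**Working it through.** **1. The plan's own sample size (section 2.9).** Inputs: "The improvement rate was assumed to be 78% for the control group and 92.5% for the treatment group"; two-sided 0.05; 80% power; 1:1 allocation; 20% dropout. With unpooled variance:

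n = (1.960 + 0.842)² × [0.78×0.22 + 0.925×0.075] / 0.145² = 89.96, so 90 per arm and 180 in total. Then 90/0.8 = 112.5, so 113 per arm and 226. The stated figures reproduce.

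The standard error of the difference at 90 per arm is √[(0.1716 + 0.0694)/90] = 0.052, or 5.2 points.

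**2. How strongly the hurdle could act.** The documents do not give the mix of symptom counts, so this is an assumption: equal thirds with 2, 3 and 4 symptoms, and independent symptoms that each improve with probability q. Response is then

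- two symptoms: q²
- three symptoms: 3q² − 2q³
- four symptoms: 1 − (1−q)⁴ − 4q(1−q)³

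Setting the average to 78% gives q = 0.745 and control response of 55.5%, 83.8% and 94.6%. Setting it to 92.5% gives q = 0.899 and 80.8%, 97.1% and 99.6%.

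**3. Effect on power, three count strata.** 90 per arm, equal mix, overall rates held at 78% and 92.5%, 40,000 simulated trials per scenario, no age strata:

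| Chance of improvement per symptom | Within-patient correlation | Control response, 2/3/4 symptoms (%) | Power without count (%) | Power with count (%) |
|---|---|---|---|---|
| Equal | 0 | 55.5 / 83.8 / 94.6 | 80.0 | 85.1 |
| Equal | 0.2 | 62.4 / 81.8 / 89.8 | 80.3 | 82.3 |
| Equal | 0.4 | 67.6 / 80.4 / 86.1 | 80.3 | 81.0 |
| Log-odds −0.6 per extra symptom | 0 | 69.4 / 82.4 / 82.2 | 80.4 | 81.1 |
| Log-odds −0.6 per extra symptom | 0.4 | 79.1 / 79.9 / 74.9 | 80.5 | 80.1 |

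With equal chance and five different count mixes, the gain is about 0 to 5 points. Type I error of the test without count strata is 4.7 to 5.1% in those equal-chance scenarios. With six strata (two assumed age groups by three counts) and an equal mix, power falls as much as 1.6 points below the unstratified test in some scenarios with falling chance.

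**4. Effect on power, the four-stratum version.** Two assumed age groups by 2 versus 3-4 symptoms, 90 per arm, 33 to 60% of patients with two symptoms, correlation 0 or 0.3, 20,000 trials per scenario:

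- equal chance per symptom: gain of 1.0 to 4.5 points
- chance falling with count: −0.5 to +2.1 points; a further run of the same design gave −0.7 to +1.2
- type I error of the four-stratum test: 4.6 to 5.2%

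**5. Chance imbalance.** If 40% of patients have two symptoms, the standard error of the between-arm difference in that share is √(0.4 × 0.6 × 2/90) = 0.073. A response gap of 25 to 30 points turns one such standard error into 7.3 × 0.25 = 1.8 to 7.3 × 0.30 = 2.2 points. Across the scenarios of step 3 the SD of this component is 0.2 to 1.9 points.

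**6. Cell sizes.** With two equal age groups and half the patients in the 3-4 group, a cell holds 90/4 = 22.5 patients per arm. In the independent-symptom case about 99% of active patients in that group respond, which leaves about 0.2 expected non-responders per active cell.

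**The case against.** The case against is strong. CMH and stratified Newcombe over the randomisation factor is a standard analysis that matches the randomisation, and nothing in section 2.10.3 is misstated. The endpoint fixes the hurdle, not the strength of the association: patients with more symptoms may be sicker and improve less per symptom, and then the gain disappears. The right yardstick for chance imbalance is the standard error of about 5 points, not the 14.5-point effect; imbalance is part of that sampling error and already covered by the test and interval. Finer strata leave cells with almost no non-responders. An adjusted sensitivity analysis may also stand in an analysis plan that is not shown.

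All of this stands as a limit on the size of the benefit, and it rules out two stronger readings. A reader might infer that the age-only test is biased or invalid. It is not: the estimate is unbiased over randomisation, and type I error stays near 5% in the scenarios checked. A reader might also infer that the trial is underpowered. The stated size reproduces, and simulated power without the adjustment is about 80%.

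The objections do not show that the adjustment does harm. In the four-stratum form the worst result was a loss of 0.7 points. The point also does not rest on silence, because section 2.10.3 itself ties the primary test and interval to the randomisation factor.

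**Conclusion.** The point holds as an efficiency improvement. The possible gain (up to 4.5 power points) is larger than the possible loss (under 1 point, if symptom count turns out not to be prognostic), and removing count imbalance as a source of error is a modest further benefit.

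The size cannot be pinned down from the documents. It depends on the mix of symptom counts at entry, on the within-patient correlation of improvement, and on whether patients with more symptoms improve less per symptom; none of these is given. The four-stratum layout also assumes two age levels, which the article does not state. It would go too far to say that symptom count drives the outcome by construction, or that power is certainly being lost.

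**What to change.** Prespecify baseline symptom count (2 versus 3-4) as an added stratum, next to age, in the primary CMH test and the stratified Newcombe interval. State a pooling rule in advance for sparse strata, for example collapsing the two count levels within the affected age stratum so that the randomisation factor is kept. Use two count levels rather than three, to avoid the sparse six-stratum layout. Keep the age-only analysis as a sensitivity analysis and leave the sample size as it is.

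Timing is the main constraint. Enrolment began in January 2023 (2.2.1), and section 2.10.5 plans an unblinded interim analysis at 114 patients with sample size re-estimation; the documents do not show whether it has taken place. The change should be fixed before any unblinded data are seen. If they have been seen, keep the age-only analysis as primary and report the adjusted one as supplementary only.

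The cost is a sentence or two in the analysis section, with no added patients, visits or measurements. The downside is smaller strata, some with few non-responders.
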